## 9 Recruitment and Retention Procedures

### 9.1.1 Recruitment Procedures

Adaptation and assessment of a common element treatment protocol designed to improve mental health in forcibly displaced populations

Version 1, September 17, 2024

We will implement opt-in and opt-out recruitment procedures. To do so, we will utilize the support of several institutions: NGOs active in migration, health centers and community mental health centers from different areas of the city, shelters that receive migrants, schools. With their agreement we will carry out the following opt-in recruitment activities:

- Posters will be posted in the front of these organizations describing the study
- Flyers will be made available at these institutions
- Flyers will be handed out at community events organized by NGOs active in migration
- Posts will be published in the social networks of NGOs active in migration

Furthermore, in coordination with NGOs that offer mental health services to Venezuelan migrants, we will ask them to identify potential eligible subject, who - due to a lack of resources - could not be offered support by the NGO. We will ask these organizations to directly reach out to these individuals to provide information about the study and give them the opportunity to learn more by a follow-up call by the research team or not (opt-out procedure). In the follow-up by the research team, individuals are explained about the study. If the person is interested in participating, the screening consent discussion will be conducted followed by the screening procedure. Eventually, we will ask participants to hand-out flyers to acquaintances that could be interested in hearing about the study and let them know that they can contact the research team directly. The script for the recruitment call can be found in the Appendix.

The posters, flyers, publications and verbal communications (e.g. the script for the recruitment call) about the study will include information on the purpose of the study, the eligibility criteria, the commitments, the online modality of the intervention, the contact information. See Appendix.

### 9.1.2 Retention Procedures

This study requires long-term subject participation; therefore, some actions will be undertaken to promote retention. Participants will receive a phone call one day prior to their session as a reminder. If a participant does not connect to the session's link, we will call them 5 minutes after the session time has ended to learn of any unforeseen difficulties and reschedule if necessary. If they don't answer, we will call and text them again the next day and a week after. Also, collateral contact information will be collected to be able to contact them for the 6-month follow-up assessment, in case they have changed phone numbers. Furthermore, to motivate completion, a participant reimbursement (5USD\$, apx 20PEN per session attended) in form of a digital giftcard will be sent at the end of the last session via WhatsApp. Lastly, rules regarding rescheduling and no-show will be agreed upon with each participant at the beginning of the intervention. In the preparatory phases of this study, we have learned that Venezuelan migrants living in Lima have long working hours and numerous responsibilities towards their families, both in Lima and in Venezuela. Thus, they have very limited time to invest in any other activity and need a certain degree of flexibility to attend to their sessions. Therefore, we hope that by addressing this at the beginning of the intervention and reaching agreements as to how to proceed, we might promote retention. However, a general rule will be set in place and participants will be told that if they can re-schedule a maximum of three sessions in a row and of six sessions overall throughout the intervention. Otherwise, they will be excluded from the study.

## 10 Screening Procedures

Since the study's main objective is to test the efficacy of an intervention in the treatment of CMD, it is a pre-requisite for participation that individuals present CMD symptoms. Therefore, a screening procedure is necessary. A call will be scheduled with potential participants that contact the research team (opt-in recruitment) or that consent to be contacted by the research

Adaptation and assessment of a common element treatment protocol designed to improve mental health in forcibly displaced populations Version 1, September 17, 2024  
team (opt-out recruitment). In this call the intervention will be described in greater detail (purpose, duration, modality) and the screening consent procedure will be carried out. Potential participants will be informed that:

- This is a research study.
- It is necessary to gather some information to be able to see if the study is suitable for the person.
- A prior requirement is to answer some questions regarding different distressful experiences.
- Based on pilot testing of the assessment, we expect the screening procedure will last no more than 30 min and will be carried out via a telephone call.
- Following completion of the questionnaires the research team will complete a follow up call.
  - Based on responses on the measures/scores, the call will either invite the participant to participate in the research project, or in the case the person is not invited, they will be called and be provided referrals to other organizations that could be able to help them.
- In case the person is invited, they will be randomly assigned to receive treatment now or in 12 weeks.
- Measures will be taken to guarantee confidentiality and data safety (specific actions will be described).
- They can decide to terminate participation in the screening procedure at any time without any negative consequence to them.
- Their participation in the screening is not tied to their participation in the study. Despite taking part in the screening, they can decide not to participate in the study.

Once this information has been delivered and questions have been clarified, we will collect informed consent for the screening. To this end, participants will receive a secure link to REDCap. Upon consent, participants will be asked questions regarding age, nationality, date of arrival to Peru, suicidality, homicidality, psychosis and the items of the PHQ9, GAD7, LEC5 and PCL5. The researcher will walk the person through the questionnaires during the call, read the questions and mark their answers. If no exclusion and all inclusion criteria apply, individuals will receive a message inviting them to participate in the study. Otherwise, they will be communicated that they cannot be included in the study and information on organizations offering mental health support will be shared with them. If suicidality or homicidality is identified, a safety plan will be implemented. Individuals will be told that their safety is at risk and that we need to contact family member. We will contact a family member and refer to the hospital or other relevant care options, such as the Community Mental Health Centers. Furthermore, individuals will be advised to call the hotline 113 to get in touch with counselors from the Peruvian mental health system.

The Screening Consent Form is attached to this Protocol in a separate document.

## 11 Consent Procedures

Since the participants targeted in this study are over 18 years old, they will give their consent themselves in an electronic informed consent procedure. The process will take place remotely. A call will be scheduled between a member of the research team and the individuals that have been identified as suitable in the screening process.

During the call, a REDCap secure link to the consent form will be sent to the potential

Adaptation and assessment of a common element treatment protocol designed to improve mental health in forcibly displaced populations

Version 1, September 17, 2024

participant and a trained member of the research team will describe the study in non-technical terms in Spanish. Study staff will receive information on the necessary procedures to obtain informed consent, and training and supervision will be repeated to continuously reinforce these procedures. All study staff will also receive training on the ethical conduct of research with human subjects and must recertify annually.

All individuals will be informed that they can withdraw their consent to participate at any time during the study, without any consequences. Potential participants will be informed that the information provided through consent and in the sessions is confidential (i.e., will not be shared with anyone outside the research team) and voluntary (i.e., they are not obligated to share it). The research staff member will emphasize that participation in the study is entirely voluntary, that participants can withdraw their consent and leave the study at any time. The research staff will receive comprehensive training to ensure that participants give their informed consent voluntarily. If at any point the potential participant is not interested in the study, the research staff member will thank them for taking the time to learn about the study and then register the information about why they were not interested in participating.

The informed consent form will provide the following information comprehensively: (a) introduction to the consent process, explaining the consent form and compliance with institutional policy and country laws; (b) reminder that participation is voluntary; (c) nature and purpose of the study; (d) explanation of study procedures; (e) potential discomforts and risks, as well as plans to protect participants from these risks; (f) potential benefits; (g) confidentiality, including how the data will be used and how it will be kept private; (h) refusal/withdrawal, including the right to withdraw consent and leave the study at any time; and (i) rights and complaints. A summary of each section will be read to the participant by the member of the research staff. After each main section, the member of the research team will pause and check comprehension, for example, by asking the participant to repeat, in their own words, what "the right to refuse" means.

Once questions have been clarified and all information has been shared, individuals will be invited to decide whether they want to participate and to give their consent electronically via a link in REDCap. In REDCap they will find the consent form, an affirmation that they understand the study and consent to participate, a box to enter their name and a box to enter the date. Also, they will find two boxes to check, if they give their permission to be contacted again by the research team for the purpose of this study and for other studies. They will be reminded that they can withdraw at any time and referred to the contact information to do so. After the call, participants will be sent a PDF copy of the signed consent form via WhatsApp.

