## 6 Potential Risks and Benefits

### 6.1 Risks

It is unlikely that participants will be at risk of physical harm as a result of the study participation. The primary risks to participants are breach of confidentiality, fatigue or personal discomfort during the intervention sessions or assessments. Participants may find some of the topics addressed during the sessions or some of the questions asked during assessments to be emotionally upsetting and may experience short-term elevations in negative affect during active intervention sessions. As with any study of participants with mental illness, there is always the risk of symptom worsening. The weekly assessment of symptoms throughout the intervention will allow us to closely monitor any changes in the migrant participants and put in action a safety plan, in case of increased severity or suicidality. Weekly meetings with supervisors, who will be closely accompanied by the research team in weekly group meetings, will enable us to timely identify participants whose symptoms are not progressing as expected and to take timely action. At any point in the study if participants exhibit increasing severity of psychiatric symptoms that warrants a higher level of care, they will be referred to the local hospital. If symptoms require immediate medical management, participants’ family members will be contacted and recommended to bring the participant to the hospital emergency room.

Adaptation and assessment of a common element treatment protocol designed to improve mental health in forcibly displaced populations

Version 1, September 17, 2024

Furthermore, participants will be advised to call the hotline 113 to get in touch with counselors from the Peruvian mental health system or the number 106 in case they need an ambulance.

In the case of the provider participants, they may find some of the topics addressed during the sessions to be emotionally upsetting or may experience concern regarding the wellbeing of some participants. As mentioned above, frequent meetings with supervisors, closely accompanied by the research team, will enable us to discuss these concerns, to identify if the symptoms of a participant are not progressing as expected and to take timely action. Also, supervisions will provide with the opportunity to tackle the discomfort that a provider might be experiencing and to find means to alleviate it.

Other measure to be taken to protect the participants against risk are the following:

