### 7.2 Subject Exclusion Criteria

Participants with suicidality, homicidality and psychosis will be excluded from the study. An individual is excluded from the study if they endorse suicidal or homicidal thoughts in the past

Adaptation and assessment of a common element treatment protocol designed to improve mental health in forcibly displaced populations  
Version 1, September 17, 2024  
three months, or a lifetime psychosis diagnosis:

- Suicidal ideation: “When someone feels as upset as you do, they may have thoughts that life isn’t worth living. What thoughts have you had like this? Have you had these thoughts in the past three months?”
- Homicidal ideation: “When someone feels as upset as you do, they may have thoughts about hurting the person who has upset or hurt them. What thoughts have you had like this? Have you had these thoughts in the past three months?”
- Psychosis: “Do you have a diagnosis of psychosis or schizophrenia?”

If an individual endorses one of these items they will be referred to relevant care options.

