### 13 Assessment of Safety and Data Safety Monitoring Plan (DSMP)

#### 13.1 Definitions for Safety Assessment

The following definitions will be used in the assessment of safety:

An *Adverse Event (AE)* is any negative outcome that is undesirable and unintended, resulting from a participant's involvement in a study. These events can encompass various forms of harm, including physical, psychological, social, legal, or economic impacts. For instance, in social-behavioral research, an example of an adverse event could be a breach of confidentiality, where a participant's private information is disclosed to individuals not involved in the research team.

An *Unanticipated Problem (UP)* is defined as an adverse event that meets three specific criteria:

1. **Unexpected Nature:** The adverse event must be unexpected, meaning its nature, severity, or frequency is inconsistent with the known or foreseeable risks described in the research protocol, informed consent documents, or other relevant sources.
2. **Relatedness to Research:** The adverse event must be related or possibly related to participation in the research. This means there is a reasonable possibility that the event was caused by the research procedures.
3. **Increased Risk of Harm:** The adverse event must suggest that the research places subjects or others at a greater risk of harm than previously known. This assessment involves considering whether the event indicates a new risk that was not anticipated based on prior knowledge of the research and its procedures.

*Serious Adverse Event (SAE)* is any adverse event that

- (1) results in death;
- (2) is life-threatening;
- (3) results in inpatient hospitalization or prolongation of existing hospitalization;
- (4) results in a persistent or significant disability/incapacity;
- (5) results in a congenital anomaly/birth defect; or

*Life-threatening* means that the event places the subject at immediate risk of death from the event as it occurred.

*Unanticipated Problem* is defined as an event, experience or outcome that meets **all three** of the following criteria:

- is unexpected; AND
- is related or possibly related to participation in the research; AND
- suggests that the research places subjects or others at a greater risk of harm (including physical, psychological, economic, or social harm) than was previously known or recognized.

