Information collected as part of this study could reveal symptoms of major depression and suicidal tendencies. All staff will be trained to identify participants who may have acute attacks of anxiety, emotional distress, or suicidal ideation. Throughout the period of interaction with participants, trained staff members will evaluate and be attentive to the emotional state of the participants and lay person therapists. All staff will be trained by the principal investigator in monitoring, evaluating, and reporting any concerns or mental health events. The wellbeing of participants will be assessed in sessions with providers and via validated measures of depression, anxiety, and PTSD provided through the intervention. The wellbeing of lay person therapists will be assessed via supervision sessions with lay person supervisors, study staff supervisors, and the principal investigator [name]. All staff must complete human subject research training offered by Boston University Medical Campus and the Collaborative Institutional Training Initiative (CITI Program). All study staff must also complete the Good Clinical Practice training offered within CITI Program. [name] has completed Good Clinical Practice Training (Principal Investigator Role: What Every New and Seasoned PI Needs to Know about the Conduct and Oversight of Clinical Research conducted by the Clinical Research Resources Office (CRRO) at Boston University, March 10th, 2023, 3.5 hours), and will complete the refresher course as needed. These extensive and required trainings meet NIH requirements for human subject research training. [name] (Principal Investigator of the study, and Licensed Clinical Psychologist) will be available at all times through her direct phone number for questions about participants, as needed, or in case of an emergency. Participants identified as suicidal or severely depressed are provided with information about the most optimal mental health centers or those closest to the participant. In accordance with the Mental Health Law, the confidentiality and voluntariness of going to a mental health center is guaranteed.

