## 14 Data Handling and Record Keeping

### 14.1 Confidentiality

As indicated in our research plan, we will do our best to protect participant data in accordance with national confidentiality laws. Participants may be at risk if they reveal a mental disorder in the discussion and their data is leaked (e.g., the social consequences of having a stigmatized disorder). For this reason, we have drawn up strict guidelines on protecting participant confidentiality. All cases of social harm and other adverse events will be brought to the attention of the mentors and the Principal Investigator. Cases of social harm that are determined to be UP, unexpected and serious (or could pose increased risk to subjects), and possibly related to being in the research will be reported to the BMC IRB, the Universidad del Pacífico, and the National Instituted of Health.

Participants will be assigned a unique study ID, with study data associated only with these IDs. Participants will be identified in all study materials solely by participant number, visit number, and visit date. A master list of participants' names and study IDs will be kept in a locked filing cabinet separate from other data. The principal investigator and research study coordinators will be the only individuals with access to this list. The master list will be destroyed at the end of the study. Transcriptions for the assessment of fidelity will use participant numbers, not their names. By recording study data in this manner, the information can be considered "de-identified," thus complying with the Health Insurance Portability and Accountability Act (HIPAA) Privacy Rule standards for individually identifiable health information.

Only the research staff will have access to participants' identifiable private information. No additional contact or data collection will be undertaken for the proposed research. All data is

Adaptation and assessment of a common element treatment protocol designed to improve mental health in forcibly displaced populations  
obtained specifically for research purposes.

Version 1, September 17, 2024

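### The Section 11 consent script promises that nothing said at consent or in sessions leaves the research team, but Section 6.1 plans emergency contact with family members and no section states the exception

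*Protocol*

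**What the plan says.** **What people are told about confidentiality**

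- Section 11 (Consent Procedures), addressed to people already found suitable at screening: what they disclose during consent and in sessions "is confidential (i.e., will not be shared with anyone outside the research team". No exception follows.
- Section 14.1 (Confidentiality): "Only the research staff will have access to participants' identifiable private information". No exception follows.
- Section 10 (Screening Procedures), in the list of points given before screening: steps will be taken to guarantee confidentiality, and those steps will be described. The list mentions no limit and no possible contact with family.

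**What the safety plan does**

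- Section 6.1 (Risks), for enrolled participants: worsening severity leads to hospital referral. If immediate medical care is needed, "family members will be contacted and recommended to bring the participant to the hospital emergency room".
- Section 10, if suicidality or homicidality is found at screening: "Individuals will be told that their safety is at risk and that we need to contact family member". The text continues: "We will contact a family member and refer to the hospital or other relevant care options".
- Section 7.2 (Subject Exclusion Criteria), for the same screening answers and for psychosis: "If an individual endorses one of these items they will be referred to relevant care options". Family is not mentioned.
- Section 13.1, for participants identified as suicidal or severely depressed: they receive information about mental health centers, and under the Mental Health Law "the confidentiality and voluntariness of going to a mental health center is guaranteed". Family is not mentioned.

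**How a breach is classified**

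- Section 13.1 defines an adverse event as a negative outcome that is both undesirable and not intended. Its example is a breach of confidentiality in which a participant's "private information is disclosed to individuals not involved in the research team".

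**The concern.** The Section 11 wording does more than promise discretion. It explains confidentiality as no sharing beyond the research team. Family members are outside the research team, and the protocol's own emergency procedure contacts them. A participant could disclose a crisis in a session on the strength of that assurance and then find that a relative has been called.

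This bears on informed consent and on trust, for people who may be in crisis when they disclose. Section 6.1 puts breach of confidentiality first among the primary risks, and Sections 3.1 and 6.1 both foresee suicidality arising during the intervention. The case is therefore one that the plan expects to meet. Staff also need to know whether a planned safety contact is to be recorded as a breach, and Section 13.1 does not say.

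**Working it through.** No arithmetic applies. The check sets the sections side by side, by stage.

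| Stage | Assurance given | Planned action | Compatible as written? |
|---|---|---|---|
| Screening | Section 10: steps to guarantee confidentiality, no limit listed | Section 10: family contact if suicidality or homicidality is found | Not a direct contradiction, but the limit is disclosed only after the answers are given |
| After enrollment | Section 11: no sharing outside the team. Section 14.1: access for research staff only | Section 6.1: family contact if immediate medical care is needed | No |

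1. **Scope of the Section 11 promise.** It covers information from consent and from sessions. Risk that emerges in a session falls inside it. Risk that emerges only from a REDCap questionnaire is arguably outside its literal scope, but falls under the access sentence in Section 14.1 if it is identifiable.
2. **Does the Section 6.1 contact share information?** Relatives are asked to take the participant to an emergency room. That request conveys that the participant's condition is urgent. If the team learned this in a session, information covered by Section 11 has reached someone outside the team.
3. **Can both be carried out?** No. Staff who make the contact depart from Sections 11 and 14.1; staff who keep to those sections cannot make the contact.
4. **Screening.** People who endorse suicidal or homicidal thoughts are excluded under Section 7.2, so on the protocol's sequence they do not reach the Section 11 statement. The Section 10 statement made to them is softer. The gap is one of timing: the pre-screening list names no limit, and the person is told of the family contact once the risk has been identified.
5. **Descriptions of the response.** Sections 7.2 and 13.1 do not forbid family contact. They omit it. Referral, information about centers and family contact could all be done for one person, but a reader of Section 7.2 or 13.1 alone would not learn that Section 10 or 6.1 adds a contact.
6. **Adverse event status.** A planned safety contact matches the words of the Section 13.1 example, because someone outside the team receives private information. It does not match the definition above the example, because it is deliberate. The protocol does not say how to record it.

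**The case against.** The strongest reply has four parts.

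**The consent forms may already state the exception.** Section 11 says that the participation form covers plans to protect participants from risk, and confidentiality. The screening form is a separate document. Neither is shown, so a reader who infers that participants have in fact been misled goes further than the documents allow. This limits the conclusion but does not remove it. Section 11 is current text on what staff say. A form that states an exception would disagree with Section 11, and a form without one would disagree with Section 6.1.

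**Screening contact does not break the Section 11 promise.** A reader might pair the Section 10 family contact with the Section 11 statement. They apply to different people at different stages, and the person screened is told of the contact. This stands. The direct conflict is Sections 11 and 14.1 against Section 6.1.

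**The safety plan does not itself produce an adverse event.** A reader might infer this from the Section 13.1 example. The definition requires an unintended outcome, and a planned protective contact is intended. This stands. What remains is that the protocol does not separate planned disclosures from breaches.

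**Section 13.1 does not promise silence towards family.** Its guarantee concerns attendance at a mental health center. Read that way it does not contradict Section 10 or 6.1, and it is not shown that staff are unable to follow Sections 7.2, 10 and 13.1 together. This stands.

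A reader might also suppose that the relative contacted could be the person involved in a conflict, because Section 8 lists domestic violence organizations among referral options. That mention is only an example of a referral destination, and nothing in the documents supports the further step.

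**Conclusion.** The point holds for the protocol's wording. Sections 11 and 14.1 state confidentiality without exception, and Section 6.1 plans a disclosure that contradicts them for enrolled participants. At screening, Section 10 gives no limit in advance of the questions that can trigger family contact. Sections 7.2 and 13.1 leave that contact out.

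On size, the Section 11 statement is made to everyone who consents, so to all 90 planned migrant participants (60 intervention and 30 waitlist). How many would meet the Section 6.1 trigger cannot be estimated. The documents give no rate, the trigger is a need for immediate medical care and not any report of suicidal thoughts, and recent suicidal or homicidal thoughts are exclusion criteria. The contradiction arises with the first such case.

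The conclusion assumes that staff follow Section 11 as written and that family members are not part of the research team. It does not affect randomization, the outcome measures or the analysis. It should still be corrected, because it has staff give an untrue assurance to people at risk.

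**What to change.** 1. Reconcile Sections 6.1, 7.2, 10, 11, 13.1 and 14.1 on the response to suicidality, homicidality and acute deterioration. Which contact rule applies is for the sponsor and the IRBs to decide.
2. In Section 11, replace the unqualified assurance with a statement of the limits of confidentiality that matches the rule retained. Bring the access sentence in Section 14.1 into line.
3. Add the same statement to the Section 10 list of information given before screening, so that people hear it before they answer.
4. State in Section 13.1 that a planned disclosure under the safety plan is recorded separately from a breach of confidentiality.
5. Check both consent forms against the new wording.

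The cost is protocol text, two consent scripts and an IRB amendment. There is one small downside: some people may disclose less once they know the limit.
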